### Trial design (8)

This is a three-armed, parallel-group RCT, estimating the efficacy of a guided transdiagnostic, tailored internet treatment program for mild to moderate depression and anxiety, and of an unguided version of the same program. The efficacy of each of these programs will be estimated in comparison to a waitlisted control group. In a SWAT, participants in the guided and unguided arms of the trial who show no short-term benefit from the treatment, are included in a secondary randomization to an ATS entailing additional guidance (the guided arm) or standard guidance (the unguided arm). The study also encompasses qualitative evaluation of the treatment experience.

## Methods: participants, interventions and outcomes

### Study setting (9)

Participants will be recruited from among university students who have responded to the online baseline WHO-WMH-ICS survey [3] in Sweden in their first term of study. Recruitment to this study takes place early in the respondents’ second term of studies via a brief additional online survey of treatment eligibility. Annual follow-ups to the WHO-WMH-ICS survey take place, allowing for expanded recruitment to include invitation to survey respondents in their 4th or 6th term of study. Students are recruited at all participating universities, 15 at this writing (see https://iterapi.se/puma).

### Eligibility criteria (10)

The inclusion criteria for the main trial are as follows: self-report of mild to moderate depression and/or anxiety, operationalized as a score of at least 5 and up to and including 19 points on the 9-item Patient Health Questionnaire (PHQ-9) [29]; and/or a score of at 5 or more points on the 7-item General Anxiety Disorder questionnaire (GAD-7) [30]. The SWAT inclusion criteria are listed under SPIRIT item 11b.

The exclusion criteria for the main trial are, in the following order:Current engagement in psychological treatment; and/orHaving initiated medication for depression and/or anxiety within the 3 weeks prior to completing the recruitment questionnaire.Scores that are (a) below (too mild) or (b) above the inclusion thresholds on PHQ-9 or GAD-7 (too severe). The latter participants are asked to provide their telephone number to the study management if they would like a telephone counseling session with the PI or co-PI; orScores of 2 or 3 on the suicidal ideation item 9 in the PHQ-9; orScores on the DSM-5 CCSM short-form questionnaire [31, 32] of (a) 3 or more on the DSM-5 suicide question (domain VI, item 11), (b) and/or scores of 2 or more on one or both of the DSM-5 psychosis questions (domain VII, items 12 and 13); (c) and/or scores of 3 or more on one or both of the DSM-5 alcohol/drug questions (domain XIII, items 21 and 23).

Participants who fulfil exclusion criteria 1 or 2 do not complete the PHQ-9 and GAD-7. Participants who do not fulfill exclusion criteria 3 or 4 complete the DSM-5 CCSM short-form questionnaire for further assessment of exclusion criteria 5a-c.

### Who will take informed consent? (26a)

Informed consent will be collected electronically, via the online treatment eligibility screening survey, accessed following invitation to participate in the study. This consent form includes participation in the SWAT, as well as possible future invitations to participate in individual qualitative interviews. Consent to participate in the baseline online WHO-WMH-ICS survey has been provided earlier, including the option to consent to future linkage with higher education outcome data from the national Ladok student registry.

### Additional consent provisions for collection and use of participant data and biological specimens (26b)

Not applicable. No biological specimens are collected.

## Interventions

### Explanation for the choice of comparators (6b)

The primary comparator for the guided and unguided intervention groups is the waitlisted control group, which gains access to the unguided version of the intervention 6 months after randomization. The secondary comparator for the guided intervention group is comparison with the unguided group. The justification for this is given in the “Background and rationale (6a)” section.

### Intervention description (11a)

The intervention, titled “PUMA,” is offered to participants in all three of the trial arms and consists of eight treatment modules based on CBT, all delivered over 8 weeks via the iTerapi internet treatment platform at Linköping University [33]. Participants are recommended to work with one module per week. Modules 1, 7, and 8 are standard for all, and focus on psychoeducation, acceptance of one’s thoughts and feelings, and on strategies for self-care. The content for modules 2 and 3 depends on the participant’s choice of a depression- or anxiety-focused track and focuses on behavioral activation or exposure-based strategies, respectively. Modules 4, 5, and 6 are tailored choices from a menu of eight additional elective modules. The modules in the elective treatment menu were selected in view of evidence that university students display treatment needs related to emotion regulation, cognitive thought management, stress management, relaxation, problematic sleep patterns, social anxiety, panic anxiety, and perfectionism. Participants maintain unguided access to the program content for 2 weeks following the 8-week program. Versions of the modules used in this trial were evaluated in two earlier studies [34, 35] as well as in a more recent study evaluating self-selected tailoring as compared to clinician-selected tailoring, with a somewhat more positive outcome for the self-selected procedure [25]. For this trial, existing module content was thoroughly reviewed and revised, for adaptation to the student target group, to improve language clarity and to reduce repetition. Table 1 displays an overview of the treatment content.

**Table 1 Tab1:** Intervention modules in the “PUMA” transdiagnostic, tailored ICBT program for students

Week	Module type	Theme	Title
**1a. Overview**			
1	Standard^a^	Psychoeducation	It’s about you
2	Track choice^b^	Behavioral activation I	Map your activities
2	Track choice^b^	Anxiety and GAD	Anxiety and constant worry
3	Track choice^b^	Behavioral activation II	Change through action
3	Track choice^b^	Anxiety and exposure	Anxiety
4	Tailored choice^c^	Rank #1	
5	Tailored choice^c^	Rank #2	
6	Tailored choice^c^	Rank #3	
7	Standard^a^	Acceptance	Acceptance
8	Standard^a^	Maintenance	Continue to take care of yourself
**1b. Tailored choice. All elective module options are presented to participants at the start of their treatment program. The participant then ranks the top three preferences.**			
N/A	Tailored choice^c^	Emotion and affect regulation	Everything we feel
N/A	Tailored choice^c^	Cognitive restructuring	Change your thoughts
N/A	Tailored choice^c^	Stress management	Manage stress
N/A	Tailored choice^c^	Relaxation	Relaxation
N/A	Tailored choice^c^	Sleep hygiene	Change your sleep
N/A	Tailored choice^c^	Social anxiety	Anxiety and social contact
N/A	Tailored choice^c^	Panic anxiety	Anxiety and panic
N/A	Tailored choice^c^	Perfectionism	Being perfect?

Note: Each participant’s individual treatment plan is manually coded onto the platform following randomization. For all participants, access to standard and tailored materials is given automatically, in sequence

^a^Standard: The module is provided to all participants

^b^Track choice: The module is assigned on the basis of the participant’s main problem area

^c^Tailored choice: The participant selects three modules. Access is provided manually by the guide assigned to the participant, both for the guided and unguided groups

In both the guided and unguided arms of the intervention, a guide with basic CBT skills will provide an initial telephone conversation to offer each participant an opportunity to prepare for the treatment and, optionally, to consider which of the depression or anxiety tracks to select and which three elective modules to choose. For participants in the unguided arm, the self-help nature of the intervention will be explained, and information will be given that technical questions will be answered by the treatment site support team, and that any questions about the research project should be directed to the principal investigator. Participants in the waitlist arm will be offered the self-help version of the intervention 6 months after recruitment. No initial telephone conversation will be offered waitlist participants.

Guides, hereafter also referred to as therapists, are clinical psychology students at the master’s level, or healthcare professionals with basic knowledge of CBT. Therapist guides will all be concurrent participants in a remotely delivered 11-week university-level course on psychological treatment delivered via the internet; they will deliver the treatment as part of the clinical practicum within the course. Prior to initiating treatments, therapists will complete a study-specific practical training workshop on conducting online-CBT treatment, including a study-specific treatment manual. During the treatment practicum, therapists will receive 10 weekly 90-min group supervision sessions by a licensed psychologist with experience in offering internet treatment. Throughout the treatment period, therapists will refer continually to the treatment manual and guidelines, including checklists for weekly tasks. Thereafter, therapists will provide regular written feedback on participant progress within 48 h, with an instruction to spend about 15–20 min per week per participant.

The adaptive treatment strategy offered within the SWAT will entail randomization of each participant qualifying for participation (see SPIRIT items 11b and 11c). Participants in both the guided and unguided arms will be eligible for the ATS. Participants in the guided arm will be offered additional personalized support, the nature of which is clarified in an additional telephone session with the therapist or, if the participant prefers, via written communication. The ATS for participants in the unguided arm will entail standard written guidance, as provided to participants in the guided arm of the RCT. Participants in the waitlist group will not be eligible for participation in the SWAT.

#### Procedure for inclusion in the SWAT

Participants will be included in the SWAT and randomized to the ATS when a risk of not benefitting from treatment is identified. The threshold for identifying risk will be calculated based on an algorithm that includes data from Timepoint 0 (T0; baseline trial eligibility screening), T1 (pre-treatment assessment), and T2 (mid-treatment assessment during the third week of treatment); see Table 2 for an overview of questionnaires included at each timepoint.

**Table 2 Tab2:** Overview of instruments used in treatment (Tx) RCT Sweden. Inspired by Weisel et al. 2019 [36]. All followups are timed from the point of pre-Tx randomization

Nr	Phase	Category	Construct	Instrument	T0 Tx eligibility assessment	T1 Pre-Tx Assessment	Weekly during Tx	T2 Mid-Tx after 3rd Tx module	T3 End of Tx (8 w)	T4 6 m follow-up	T5 12 m follow-up	T6 24 m follow-up
1	Screen	Mental health	Demographic / mental health screen	WHO-WMH-ICS	Data from 1st term						3rd term	5th term
1.1	Information	Referral	Referral	Resources	√							
2	Screen	Tx now?	Exclusion	3 Qs	√							
2.1	Screen	Mental health	Co-morbidity	DSM-5 CCSM +	√			√	√	√	√	√
3	Screen/Weekly/ primary outcome	Mental health	Depression	PHQ-9	√	√	√	√	√	√	√	√
4	Screen/Weekly/ primary outcome	Mental health	Anxiety	GAD-7	√	√	√	√	√	√	√	√
5	Screen (as long as relevant)	Mental health	Pandemic-related anxiety	GAD-7COVID	√							
6	Screen + all phases	Wellbeing	Well-being	WHO-5	√	√	√	√	√	√	√	√
7	Pre-Tx	Tx prep	Motivational component	Telephone interview		√						
8	Pre-Tx	Tx prep	Tx expectancy	CEQ		√		√				
9	Pre-Tx	Tx prep	Attitudes towards professional help	ATSPPHS		√					√	√
10	Mid-Tx assessment	Risk factor	Risk factor Sleep	ISI		√		√	√	√	√	√
11	Mid-Tx assessment	Skill	Behavioral Activation Depression	BADS		√		√	√	√	√	√
12	Mid-Tx assessment	Skill	Managing negative thoughts	SOCT-P		√		√	√			√
13	Mid-Tx assessment	Txprocess	Tx alliance	WAI-SR for internet Tx				√	√			
14	Secondary outcome	Wellbeing	Quality of life	WHOQOLBref		√					√	√
15	Secondary outcome	Risk factor	Alcohol	AUDIT-C		√			√	√	√	√
16	Secondary outcome	Risk factor	Risk factor Self-esteem	RSES		√			√	√	√	√
17	Secondary outcome	Risk factor	Risk factor Resilience	CD-RISC-25		√			√	√	√	√
18	Secondary outcome	Risk factor	Emotion regulation	DERS-16		√			√	√	√	√
19	Secondary outcome	Risk factor	Worry	PSWQ		√			√	√	√	√
20	Secondary outcome	Risk factor	Personality	BFI-10		√					√	√

21. *TIC-P* Healthcare consumption and productivity loss in patients with a psychiatric disorder (56 items); Bouwmans et al., 2013 [56]

22. *CSQ* Client Satisfaction Questionnaire (8 items), Attkisson & Zwick 1982 [57]

22.1. *CSQ, adapted* Client Satisfaction Questionnaire (8 items), adapted for mid-Tx assessment

23. *NEQ* Negative treatment effects questionnaire (20 items), Rozental et al. 2019 [58]

24. *Qualitative interview* Qualitative interview on experience of treatment intervention

The algorithm will build on data from the PHQ-9 and GAD-7 questionnaires, where data for all three timepoints will be entered for each questionnaire separately, as follows: [(T0 + T1)/2] − T2. If the outcome of the algorithm is equal to £0 for either PHQ-9 or GAD-7, or both, the participant will be randomized to the ATS, or to continue in the treatment arm to which they were assigned at the start of the main trial. See under “Interim analyses (21b)” for a more detailed description. Randomization will be conducted via SPSS version 28.0 using an outcome of the exact number of randomized individuals, stratified by group allocation to guided or unguided treatment. Participants with missing data at any of these timepoints will not be included in the SWAT since unsuccessful attempts will have already been made to encourage them to respond, and dropout from the main trial seems likely.

#### Qualitative interviews

The trial will include qualitative evaluation to obtain a deeper understanding of participants’ subjective experiences of guided, unguided, or waitlisted treatment, as well as of SWAT allocation to an ATS.

### Criteria for discontinuing or modifying allocated interventions (11b)

Lack of short-term benefit from the intervention will constitute the inclusion criterion for the SWAT. Lack of short-term benefit will be operationalized as lack of improvement or worsening of symptoms according to PHQ-9 and/or GAD-7, measured in the third week of treatment, for participants in both the guided and unguided arms. Participants eligible for SWAT participation will be included in a secondary randomization procedure. Those randomized to the ATS will receive additional human guidance if originally randomized to the guided arm, or will be given standard guidance through written secure messages, if originally randomized to the unguided arm. Participants not randomized to the ATS will continue in the original allocation to guided or unguided treatment, without any added support. Participants in the waitlist group will not be included in the SWAT.

### Strategies to improve adherence to interventions (11c)

In the guided and unguided groups, randomization to an ATS within the SWAT trial is primarily intended to minimize the risk of treatment failure. This aim includes improving intervention adherence. Additional strategies include email reminders, as well as telephone follow-ups to be initiated in the spring of 2024. As previously noted, the waitlist group will not be part of the SWAT.

### Relevant concomitant care permitted or prohibited during the trial (11d)

Throughout the trial, included participants will be free to access ordinary healthcare and/or local student mental health services as needed, i.e., seeking other healthcare resources alongside study participation is not an exclusion criterion. Within the trial, risk management and safety rules concerning suicidal ideation and/or plans have been established. In the first step, the study team will receive an automatic notification from the study platform if a participant endorses increased suicidal ideation compared to the baseline measure (i.e., a score of 2 or higher on the suicidal ideation item on item 9 of the PHQ-9, which will be administered at all assessment points). In the second step, a protocol to assess risk, provide referral resources, and discuss safety planning has been established for the study, and will be applied as follows for participants in both treatment groups: If a participant scores either a 2 or a 3 on the PHQ-9 suicide item, the treatment therapist (1) will send a message inside the study platform to assess the participant’s well-being and level of risk; (2) will communicate that the participant may receive a phone call from the therapist; (3) if the participant does not respond to the message so that risk can be assessed, the therapist will contact the participant via telephone to discuss the current situation and possible needs for referral, (4) if the therapist deems it warranted, they will contact the participant immediately by phone. Steps 1–4 will also be implemented in cases where the therapist assesses a higher risk for the participant based on communication in the platform, not conditional on raised suicidal ideation. For all steps, the principal investigator will be available to discuss severity level assessment, safety planning, and referral options on a case-by-case basis. A list of available healthcare resources in the community (e.g., student services, suicide prevention hotline, crisis text line, primary care provider) will be provided by the study as needed.

### Provisions for post-trial care (30)

Standard care is available within the national healthcare system in Sweden.

### Outcomes (12)

#### Primary outcome

The trial has two co-primary outcomes, assessed in all participants regardless of treatment received. The primary contrasts are guided vs. waiting list and unguided vs. waiting list.Anxiety, which will be measured using GAD-7 (total score).Depression, which will be measured using PHQ-9 (total score).

Although participants choose a primary treatment focus on anxiety or depression, most are expected to exhibit baseline symptoms for both disorders. For this reason, the two co-primary outcomes are assessed and analyzed among all participants.

Primary outcomes are assessed 10 weeks post-randomization (T3 post-treatment measure), 6 months post-randomization (T4), 12 months post-randomization (T5), and 24 months post-randomization (T6). After T4, participants in the waiting list control group will be offered the unguided version of the interventions; thus, we will use T3 and T4 measures for contrasts among all three groups and all follow-up interval measures for contrasts between guided and unguided groups (adjusted for baseline measures).

See Fig. 1a for a complete SPIRIT checklist, Fig. 1b for the participant timeline, Fig. 2 for a TIDieR checklist regarding the intervention description, Fig. 3 for a CONSORT flow diagram, Table 1 for an overview of the intervention modules, and Table 2 for a complete, referenced list of the assessment instrument used in the study.

**Fig. 1 Fig1:**
[figure not shown]
SPIRIT checklist (a) and schedule of enrolment, interventions, and assessments (b)

**Fig. 2 Fig2:**
[figure not shown]
TIDieR checklist for intervention description and replication

**Fig. 3 Fig3:**
[figure not shown]
CONSORT RCT flowchart

#### Secondary outcomes

The trial also has nine secondary outcomes, assessed in all participants regardless of treatment received. Following the same rationale as for the primary outcomes contrasts among all three groups will be done using measures at T3 and T4, while T5 and T6 measures will be used to contrast guided and unguided groups (adjusted for baseline measures). All secondary outcomes are listed in Table 2 in order of chronological administration to participants.Externally and behaviorally oriented outcomesAlcohol consumption, which will be measured using AUDIT-C (T3-T6).Comorbidity, which will be measured using DSM-5 CCSM (T3-T6).Resilience, which will be measured using CD-RISC-25 (T3-T6).Sleep, which will be measured using ISI (T3-T6).Well-being, which will be measured using WHO-5 (T3-T6).Internally oriented outcomesEmotional regulation, which will be measured using DERS-16 (T3-T6).Personality, which will be measured using BFI-10 (T3-T6).Self-esteem, which will be measured using RSES (T3-T6).Worry, which will be measured using PSWQ (T3-T6).Mediator outcomesBehavioral activation-depression, measured using BADS (T2-T3).Behavioral activation-depression, measured using BADS (T2-T3).

### Participant timeline (13)

See Fig. 1 for participants’ timeline through the trial including allocation to the SWAT. Qualitative interviews will be conducted starting midway through the RCT and are estimated to take about 30–60 min per interview.

### Sample size (14)

We calculated the required sample size based on the smallest effect size on primary outcomes that we did not want to miss, with respect to the contrast between the guided intervention and waiting list control at 6 months post-randomization (T4). We estimated this effect size to 0.3 Cohen’s *d*. With a significance level of 0.05 (alpha) and power of 0.8 (beta), a two-sided *t*-test would require 176 individuals per group, giving a total of 528. Assuming an attrition rate of 40% at T4, this means that we should recruit at least 880 participants. Notwithstanding this power calculation, we hope to extend our recruitment sample to up to 1200 participants if possible, given additional possible attrition after T4 and the importance of reporting outcomes over a longer term than 6 months.

Regarding analysis of the SWAT comparing adapted versus continued standard treatment for at-risk participants, earlier work evaluating for insomnia [33] suggests that between-group differences in final scores corresponding to *d* = 0.4 are possible, which would require *n* = 100 + 100 at-risk participants, i.e., well within the recruitment target.

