## Analysis

### Statistical methods for primary and secondary outcomes (20a)

We will keep participants in the groups to which they were randomized in all analyses (intention-to-treat). We will conduct both available data analyses and analyses with missing data imputed using multiple imputations with chained equations (generating 200 datasets using 30 iterations of predictive mean matching). Both available data and imputed data analyses will be used to interpret findings.

All models of primary and secondary outcomes will be estimated using both Bayesian inference and maximum likelihood estimation [59]. The former will estimate the posterior distribution over effect estimates, while the latter will be used for null hypothesis testing. We will use (half) Student’s *t* priors for covariates, fixed intercepts, and error terms (centered at 0, with a scale of 2.5 and 3 degrees of freedom). Adaptive intercepts in multilevel models will be given standard normal priors. For point estimates, we will report the median of the posterior distribution of each parameter of interest (i.e., group contrasts), along with 95% compatibility intervals defined by the 2.5 and 97.5% percentiles of the posterior distributions. We will use the posterior probability of effect and *P*-values for our scientific inference.

The two co-primary outcomes, anxiety and depression, will be standardized and modeled using a multilevel linear regression model. The models will include a time-by-group interaction with time modeled as a dummy categorical variable (0 = T3, 1 = T4, 2 = T5, 3 = T6), as will group (0 = waiting list, 1 = unguided, 2 = guided). The models will be adjusted for baseline (T1) measures of the outcome variables (respectively) using a baseline-by-time interaction term and further adjusted for age, gender, and a binary variable indicating HBTQ (0 = No, 1 = Yes). Adaptive intercepts will be added to the models at the participant and university level. The linear combination of coefficient estimates for the group and time-by-group covariates will be used as effect estimates (i.e., differences between groups at the different follow-up intervals). For our primary contrasts (guided vs. waiting list and unguided vs. waiting list), we will report effects at T3 and T4. For our exploratory contrast (guided vs. unguided), we will report effects at all four follow-up intervals.

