## Trial status

Recruitment for a pilot study, reported separately, was completed on October 19, 2021. Recruitment for the main trial began in mid-March 2022 and will continue until statistical power is estimated to have been achieved. The current protocol is version 3, dated January 30, 2024.

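### The sample size covers one test at 0.05, but the plan declares eight primary comparisons with no deciding time point, deciding analysis or success rule

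*Protocol article*

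**What the plan says.** **Sample size (14).** The calculation is made "with respect to the contrast between the guided intervention and waiting list control at 6 months post-randomization (T4"). The effect is Cohen's d: "We estimated this effect size to 0.3". It continues "With a significance level of 0.05 (alpha) and power of 0.8 (beta"), and a two-sided t-test "would require 176 individuals per group, giving a total of 528". Attrition of 40% raises this to 880, with a hoped-for extension to 1200. The section does not say which primary outcome the calculation refers to.

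**Primary outcome, under Outcomes (12).** "The trial has two co-primary outcomes, assessed in all participants regardless of treatment received". These are GAD-7 and PHQ-9. Two primary contrasts are named: guided against waitlist and unguided against waitlist.

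**Statistical methods (20a).** "For our primary contrasts (guided vs. waiting list and unguided vs. waiting list), we will report effects at T3 and T4". Maximum likelihood supplies the null hypothesis tests and a Bayesian fit supplies posterior probabilities, and both serve inference. On missing data: "Both available data and imputed data analyses will be used to interpret findings".

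**Objectives (7).** The primary hypothesis expects both active arms to be superior to waitlist. It gives no rule across outcomes or time points.

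**The concern.** The sample size describes a trial with one primary test. The outcome and analysis sections describe a trial with eight, each read through more than one analysis. The 0.05 and the 0.8 in item 14 belong to the single test, and the protocol does not say how they carry over to the primary claim.

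Two things are at stake. If any significant result among the primary comparisons may support a claim of benefit, the false-positive risk of that claim is well above 5%. If several results must succeed together, the power of the claim is below the figure that justified the recruitment target. A reader of the final report could not tell which standard applied, and the choice could be made after the results are known.

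**Working it through.** **1. Reproduce the plan's figure.** Inputs from item 14: d = 0.3, two-sided alpha 0.05, power 0.80.
- Normal approximation: n = 2 × (1.960 + 0.842)² / 0.3² = 174.4, so 175. The exact t-test gives 175.4, so 176 per group, with power 80.1%.
- 3 × 176 = 528, and 528 / 0.60 = 880. All three figures reproduce.
- At the hoped-for 1200: 1200 / 3 × 0.60 = 240 per group with T4 data, and single-test power 90.7%.

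**2. Count the primary comparisons.** 2 outcomes × 2 contrasts × 2 time points (T3, T4) = 8. At T4 alone there are 4. Repeating each on available and imputed data adds further looks, which are not counted below.

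**3. Correlations.** The two contrasts share the waitlist arm. With equal arms the covariance is σ²/n and each variance is 2σ²/n, so the correlation is 0.5. The protocol gives no correlation between outcomes or between time points. I assume 0.5 to 0.7 for each.

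**4. Error rate at unadjusted 0.05, no true effects** (simulated correlated z-statistics; the independent case is 1 − 0.95^k):

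| Tests | Independent | Assumed correlations, both tails | Favourable direction only |
|---|---|---|---|
| 8 (T3 and T4) | 33.7% | 24-28% | about 12-14% |
| 4 (T4 only) | 18.5% | 15-16% | about 7.5-8% |

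Widening the assumed correlations to 0.3-0.8 gives about 21-30% for eight tests and 14-17% for four.

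**5. Power for the four T4 tests, d = 0.3 in all four, no baseline adjustment.** The mean of each z-statistic is d × √(n/2): 0.3 × √88 = 2.81 at 176 per arm and 0.3 × √120 = 3.29 at 240 per arm.

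| Rule | 176 per arm | 240 per arm |
|---|---|---|
| All four significant at 0.05 | 54-58% | 75-77% |
| Holm over four, per-test power | 71-72% | 86% |

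**6. Effect of the planned baseline adjustment.** With baseline-to-follow-up correlation r, the residual SD shrinks by √(1 − r²). The protocol gives no r. At an assumed r = 0.5 the effective d is 0.3 / √0.75 = 0.346, and all-four power at 176 per arm is about 73-75%. For r from 0.4 to 0.6 it is about 66-84% at 176 per arm and 85-95% at 240 per arm. The error rates in step 4 do not change.

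**The case against.** **Item 14 is not false.** It states which contrast and time point it covers, is correct for them, and claims neither a family-wise 5% nor a joint 80%. That stands. The fault is the mismatch with items 12 and 20a, not the arithmetic.

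**A statistical analysis plan may hold the rule.** It may, and a bare absence of multiplicity detail would not be a finding. But this protocol declares eight comparisons as primary and gives two missing-data analyses joint standing. An all-must-succeed rule or Holm in an unseen plan would not match the power in item 14. A fixed testing order that began with the sized contrast would keep 0.05 and 80% for its first step, but item 14 would then have to name the outcome that comes first.

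**The power figures are pessimistic.** In part, yes. They use an unadjusted t-test, and baseline adjustment and recruitment towards 1200 would both help. The first depends on a correlation not given, the second is only a hope, and neither lowers the error rate.

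**Stronger readings a reader might infer.**
- *That power is about half of what is stated.* That fits only a rule requiring all eight comparisons to succeed, which no section adopts. The hypothesis that both arms are superior concerns arms, not outcomes or times.
- *That either the 5% or any useful power must be lost.* Too absolute. Holm over the four T4 tests controls the error, and if all four effects are 0.3 the chance of at least one success at 176 per arm is about 88-91%. That is not the power item 14 states for the guided contrast.
- *That recruitment could be ended on outcome results*, because Trial status ties it to estimated power. The wording is loose, but items 7 and 14 give counts, and nothing suggests outcome-based stopping.

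Whether to adjust across two treatments sharing one control is also debated. The protocol may choose, but it needs to state its choice.

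**Conclusion.** The point holds in limited form. The calculation is right for one test, but the primary analysis as written has eight, with no deciding time point, analysis or success rule. Read as any-success at unadjusted 0.05, the family-wise error is about 24-28% for eight tests and 15-16% for the four at T4, and about half that in the favourable direction. Read as all-four-at-T4, power at the 880 minimum falls below 80% on the basis item 14 itself uses. With baseline adjustment it might come close to or pass 80%, but the protocol gives no figure from which to show this.

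These sizes rest on the assumed correlations between outcomes and between times, on the 0.5 implied by equal arms sharing a control, and, for power, on d = 0.3 in every comparison. The mismatch itself rests only on the text.

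**What to change.** In 20a:
1. Name T4, the time point used for sizing, as the decision time point, with T3 supportive.
2. Test the four outcome-by-contrast hypotheses at T4 with Holm at an overall two-sided 0.05, or state that all four must succeed at 0.05 each.
3. Name one deciding analysis, for example the maximum-likelihood mixed model, with the imputed-data and Bayesian results supportive.

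In item 14, restate the power under the chosen rule. If credit is taken for baseline adjustment, give the assumed correlation.

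The cost is wording in the protocol and the analysis plan, with no change to data collection. The downside is that the stated power for the 880 minimum becomes less favourable: without baseline adjustment it would read about 71-72% per test under Holm, or about 54-58% for all four. The rule should be settled before outcome data are compared by arm.
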